## **10 STATISTICS AND DATA ANALYSES**

### **10.1 METHOD OF RANDOMISATION**

**Note this differs from the AGILE Master Protocol and is the method of randomisation to be used for this specific candidate.**

For phase I, participants will be randomised 2:1 to IV Favipiravir or SoC.

For phase II, participants will be randomised in a 1:1 ratio to IV Favipiravir or placebo.

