## 5.1 INCLUSION CRITERIA

The main trial (Phase I and II) inclusion criteria are outlined in the AGILE Master Protocol and listed below.

1. Adult in-patients ( $\geq 18$  years) with laboratory confirmed COVID-19 infection by positive polymerase chain reaction (PCR) test within 7 days of randomisation
2. Ability to provide informed consent signed by study patient or legally acceptable representative
3. Women of childbearing potential (WOCBP) and male patients who are sexually active with WOCBP must agree to use a highly effective method of contraception (as outlined in section 5.4 below) from the first administration of trial treatment, throughout trial treatment and for the duration outlined in the candidate-specific trial protocol as well as addition 14 days for women and 7 days for men after the last dose of trial treatment.

Additional criteria specific to this candidate are:

4. Group A and B (moderate to severe disease). Patients with clinical status of Grades 4 (hospitalised, no oxygen therapy), 5 (hospitalised, oxygen by mask or nasal prongs), 6 (hospitalised, on non-invasive ventilation, or high flow oxygen) as defined by the WHO Clinical Progression Scale (WHO, 2020).
5. Less than or equal to 14 days from onset of COVID-19 symptoms

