#### **Phase II sample size**

A sample size of up to 99 patients on active treatment and up to 99 on placebo, with an interim analysis after the first 66 patients is estimated to provide the 80% probability detecting the true treatment effect of 0.5 log10 reduction in viral load, and over 90% probability for the effect of 0.6 log10 reduction, (assuming a SD for change from baseline in log10 viral load of 1.5 in each group) while controlling the probability of claiming superiority while there is no difference (type I error) below 10%.

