## **Analysis**

Patients will be analysed according to the treatment to which they were randomised (efficacy population). In addition, a supplementary analysis of the primary endpoint will be conducted in all patients for whom there were no major protocol deviations that could impact treatment efficacy (to be defined in the statistical analysis plan).

The primary efficacy endpoint in phase II of the SARS-CoV-2 viral load (in log10) will be analysed using a Bayesian repeated measures model including all post-randomisation assessments up to and including Day 3. The model will adjust for treatment, baseline viral load, visit timepoint and interaction of treatment by visit, with a subject-specific random-effect and unstructured variance-covariance matrix. A non-informative (vague) prior will be used for all model parameters. Viral load data will be log10-transformed prior to analysis with treatment differences expressed on the log10 scale. If 94% of the posterior distribution of the treatment effect is below 0 (i.e. in favour of Favipiravir), the study will conclude the treatment is efficacious, at the interim or the final analysis.

For any deaths in the trial, the change in viral load will be assumed to be zero from the last measured timepoint. To assess the impact of missingness in the primary analysis due to missing data that are not missing at random (including death) sensitivity analyses will be performed. Details will be provided in the statistical analysis plan.

Once the last participant recruited completes the Day 29 assessment the data will be unblinded to allow a primary readout of this endpoint. Participants will continue to complete the remaining scheduled assessments and will not be unblinded at an individual level.

Further details on analysis methods for other endpoints will be detailed in a detailed SAP, which will be finalised and signed off prior to database lock.

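### Section 10.1 gives only a 1:1 ratio for Phase II and the primary model omits baseline WHO grade, although Grades 4 to 6 are mixed and grade is known before randomisation

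*Protocol*

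**What the plan says.** Section 10.1 opens with "Note this differs from the AGILE Master Protocol and is the method of randomisation to be used for this specific candidate". For Phase II the method then consists of one sentence: "For phase II, participants will be randomised in a 1:1 ratio to IV Favipiravir or placebo". No stratum, block scheme or minimisation factor appears in that section or elsewhere in the protocol.

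Section 5.1 admits a range of severity: "Patients with clinical status of Grades 4 (hospitalised, no oxygen therapy), 5 (hospitalised, oxygen by mask or nasal prongs), 6" (the last being non-invasive ventilation or high-flow oxygen). The schedule in 1.3 and section 8.1 place a WHO scale assessment at screening, before randomisation.

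Section 10.3.2 fixes the primary viral-load model: "The model will adjust for treatment, baseline viral load, visit timepoint and interaction of treatment by visit". Severity is not in that list. For the remaining endpoints the same section says "Further details on analysis methods for other endpoints will be detailed in a detailed SAP". The sample-size paragraph in 10.2 sets the scale: "A sample size of up to 99 patients on active treatment and up to 99 on placebo, with an interim analysis after the first 66", which means 33 per arm at the interim.

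**The concern.** The three grades run from no oxygen to non-invasive ventilation. Grade is also the starting point of the secondary improvement endpoint, a two-step change on the same scale, so it is bound to be prognostic there. A bare ratio leaves its balance to chance, and the interim at 33 per arm can stop the trial.

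Timing is why this is more than analysis-plan detail. Section 10.3.2 has the SAP signed off before database lock. An SAP can add a covariate at that point, but it cannot alter how patients were allocated, so stratification has to be settled before Phase II opens. The primary model's covariates are also already fixed in the protocol.

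At stake are a small gain in precision on the primary endpoint, and a readable interim. The DMEC also looks at safety at that point, and its tables are harder to interpret if one arm happens to be sicker.

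**Working it through.** **1. The plan's own figures.** Inputs from 10.2 and 10.3.2: 33 then 99 per arm, SD 1.5 log10, efficacy if the posterior probability exceeds 0.94, futility if it is below 0.3. With a vague prior these are z limits of 1.555 and −0.524.

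- Standard error = 1.5 × √(2/n), which is 0.369 at 33 per arm and 0.213 at 99.
- For a 0.5 log10 effect the expected z is 0.5/0.369 = 1.354 at the interim and 0.5/0.213 = 2.345 at the end. The correlation between looks is √(33/99) = 0.577.
- Chance of stopping for efficacy at the interim: 1 − Φ(1.555 − 1.354) = 42.0%.
- Over both looks: power 80.4% at 0.5 log10 and 90.4% at 0.6 log10; type I error 9.98%.

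The stated 80%, over 90% and below 10% all reproduce.

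**2. Chance imbalance in grade.** The protocol gives no grade mix, so 40/40/20% for Grades 4/5/6 is an assumption. Without stratification, each arm's count in a grade with share p is binomial, and the SD of the difference in shares is √(2p(1 − p)/n). For p = 0.4 this is 12.1 points at 33 per arm and 7.0 points at 99. Exact binomial results:

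| Share of the grade | Difference ≥15 points, 33 per arm | Difference ≥15 points, 99 per arm |
|---|---|---|
| 10% | 6% | 0.1% |
| 25% | 20% | 1.7% |
| 40% (assumed Grade 4) | 26% | 3.5% |
| 50% | 27% | 3.9% |

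At a 40% share the 95th percentile of the absolute difference is 24 points at 33 per arm and 13 points at 99.

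**3. What this does to the primary decision.** Score the grades 0, 1, 2. Under the 40/40/20 mix the variance of the score is (0.4 × 1 + 0.2 × 4) − (0.4 + 0.4)² = 1.2 − 0.64 = 0.56. Let each grade shift the Day 3 change by g beyond baseline viral load, and take 1.5 as the SD before grade is used.

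- g = 0.25: share of variance 0.25² × 0.56/2.25 = 1.6%; SD with grade in the model 1.488; two-stage power 80.4% to 80.9%.
- g = 0.5: share 0.5² × 0.56/2.25 = 6.2%; SD 1.453; two-stage power 80.4% to 82.4%.

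The gain is about 0.5 to 2 points. In a more extreme case, a 1.0 log10 shift confined to a Grade 6 group of 25%, single-look power at 99 per arm goes from 78.5% to about 81.5%.

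Under no treatment effect, simulation with neither stratification nor adjustment gives a type I error of 5.9% to 6.0% per look, against a nominal 6%.

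**4. Stratify, adjust or both.** In the 1.0 log10 case, stratifying without putting grade in the model lowers the per-look type I error to 5.3%. The model then overstates its own variance and most of the gain is lost. The two changes therefore belong together.

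**The case against.** The strongest reply is that 10.1 gives a ratio and excludes nothing. Allocation runs through the trial database and an interactive web system whose specification is not shown, so blocks or strata may exist there. This stands as far as it goes: the accurate statement is that no stratification factor is given, not that the allocation is known to be unstratified. But a section claiming to state the method should name the factor if there is one.

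A reader might also infer from the note that 10.1 differs from the Master Protocol that a severity stratum was removed. The Master Protocol is not at hand, and the difference may lie only in the ratios or arms.

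A second reply is that the primary model already adjusts for baseline viral load, that chance imbalance under valid randomisation neither biases the interim decision on average nor raises its error rate, and that the gain is small. All of this stands, and it limits the size of the point.

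Thirdly, a reader might conclude that the clinical comparisons (discharge, improvement, mortality) lose power as planned. The documents do not support that, because their methods are left to the SAP. Any such loss would come mainly from omitted adjustment. In one assumed binary example at 99 per arm (grade shares 25/50/25%, control rates 90/70/40%, odds ratio 2.2), power is 55.5% with neither measure, 56.3% with stratification alone, 60.3% with adjustment alone and 61.4% with both.

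**Conclusion.** The point holds as a modest design improvement. Section 10.1 names no stratification factor and the fixed primary model leaves out baseline WHO grade, although grade is available before randomisation and the enrolled range of severity is wide.

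A 15-point difference in the Grade 4 share at the interim is a real possibility, about one trial in four under the assumed 40/40/20 mix and 6% to 27% across grade shares of 10% to 50%. It would be wrong to call it likely. By 198 patients it is uncommon, at about 4%. Using grade gains about 0.5 to 2 points of power on the primary endpoint. The grade mix and the 0.25 to 0.5 log10 shift per grade are assumptions, since the documents give neither.

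Nothing in 10.2 needs correcting. A biased or error-inflated interim decision, or a shown loss of power in the clinical endpoints, would go beyond what the protocol supports.

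**What to change.** - **Section 10.1:** state that the Phase II allocation is stratified by the last WHO grade recorded before randomisation (4, 5 or 6), using permuted blocks. Merge Grades 5 and 6 if few Grade 6 patients are expected. If strata or blocks are already set in the allocation system, write them here.
- **Section 10.3.2:** add baseline WHO grade, in the same categories, as a covariate in the primary model.
- **SAP:** carry the stratum into the Phase II clinical comparisons when their methods are specified.

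The cost is one allocation setting, made before Phase II opens, and one model term. No new assessment is needed and the sample size is unchanged. The downside is that blocks may be incomplete in the smallest stratum. Crossing grade with site would make this worse: with up to 8 sites and 3 grades there are 24 strata, or 66/24 = 2.75 patients per stratum at the interim, so grade alone is the better choice.

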### **10.2 SAMPLE SIZE**

#### **Phase I sample size**

The sample size for phase I is not fixed. A total of up to 5 cohorts of 6 participants are planned to be dosed. However, two additional cohorts may be added. The dose in these cohorts will not exceed 2400mg (BID).

#### **Phase II sample size**

A sample size of up to 99 patients on active treatment and up to 99 on placebo, with an interim analysis after the first 66 patients is estimated to provide the 80% probability detecting the true treatment effect of 0.5 log10 reduction in viral load, and over 90% probability for the effect of 0.6 log10 reduction, (assuming a SD for change from baseline in log10 viral load of 1.5 in each group) while controlling the probability of claiming superiority while there is no difference (type I error) below 10%.

### 10.3 STATISTICAL ANALYSIS PLAN (SAP)

Refer to AGILE Master Protocol section 10.3

#### 10.3.1 Phase I

##### Study population

An evaluable patient for the study will be all patients randomised to Favipiravir, who have had at least one dose or randomised to standard of care.

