| Sample size:                            | 
Phase I:
 
The plan is to test up to 5 dose levels of IV Favipiravir in up to 5 cohorts of 6 patients each (30 patients in total). Fewer than 5 cohorts and up to 42 patients (allowing for another two cohorts of 6 participants) may be enrolled, with the final number dependent on dose escalation decisions. Each cohort includes 4 IV Favipiravir patients and 2 SoC.
 
Phase II:
 
A maximum of 198 participants, randomised in a 1:1 ratio IV Favipiravir and placebo, will be enrolled in the phase II stage. There will be a blinded efficacy and futility review after the first 66 patients (one third of the way through the trial without pausing the recruitment).
                                                                                                                                                                                   |
| Investigational Medicinal Product/s:    | 
Favipiravir: 6-fluoro-3-hydroxypyrazine-2-carboxamide, T-705
 
Phase I: IV Favipiravir or SoC (open label)
 
Phase II: IV Favipiravir or placebo (double blinded)
 
Favipiravir is a novel nucleic acid (pyrazine molecule) analogue that interferes with viral ribonucleic acid (RNA) replication and has demonstrated activity against SARS-CoV-2 both in-vitro and in animal infection models (Wang, 2020) (Suzanne, 2020).
                                                                                                                                                                                                                                                                                                                                                                                                                                                    |

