|                                                                                                                                                                                                                                                                                                                  |                                                                                                                                                                                                                                                                                                                                                                                                                                         |
|------------------------------------------------------------------------------------------------------------------------------------------------------------------------------------------------------------------------------------------------------------------------------------------------------------------|-----------------------------------------------------------------------------------------------------------------------------------------------------------------------------------------------------------------------------------------------------------------------------------------------------------------------------------------------------------------------------------------------------------------------------------------|
|                                                                                                                                                                                                                                                                                                                  | 
ventilation <math>pO_2/FiO_2 < 150</math> (<math>SpO_2/FiO_2 < 200</math>) or vasopressors
 
9. Hospitalised severe disease, mechanical ventilation <math>pO_2/FiO_2 < 150</math> and vasopressors, dialysis, or ECMO
 
10. Dead
 
 
• Mortality at Days 15 and 29
 
• Time from randomisation to death (up to day 29)
 
                                   |

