### 4.2 TRIAL PHASES

#### 4.2.1 Dose finding (phase I)

Phase I will be open-label assessing escalating doses of IV Favipiravir compared with Standard of Care (SoC). Patients in phase I will be recruited in cohorts of 6 (randomised to IV Favipiravir: SoC in 2:1 allocation ratio), with review of safety and tolerability between cohorts.

Dose-finding will be carried out as per the Master Protocol (Master Protocol section 4.2.1).

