- The following is required if not performed within 24 hours of Baseline (*results are required prior to dosing only if clinically indicated*):
  - Full blood count
  - Urea and electrolytes
  - Estimated GFR
  - Liver Function Tests
  - Uric acid
  - Urinary analysis
- Pre-Dose Blood collection for translational research
- Blood samples for PK (Blood and dried blood spot) - Day 1 timepoints of pre-dose, 0-1 hr, 2-4 hr and 6-12 hr post completion of first infusion
- Non-plasma (tears, saliva, nasal secretions) – Day 1 timepoints of 6-12 hr post completion of the first infusion
- PBMC sample - Day 1 timepoints of 6-12 hr post completion of first infusion
- Safety bloods (if clinically indicated)
- Drug administration of Favipiravir (or placebo for Phase II) IV BID dose for 7 days, by infusion over up to 1 h, to be administered in hospital
- Targeted physical examination

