##### Decision Making

Dose escalation will be based on review of safety data up to Day 8 on the safety population. Doses are deemed to be safe if the risk of dose-limiting toxicity (DLT) being at least 30% larger in IV Favipiravir than standard of care is less than 25%. Dose de-escalation for the starting dose will be reviewed by the SRC and guided by their decision depending on DLTs.

A two parameter Bayesian dose escalation model will be used to recommend the next cohort dose or the recommended phase II dose. The model will target a safe dose with an additional DLT risk of 20% (the target interval of 15-25%) above standard of care.

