##### Analyses

Please refer to the AGILE master protocol phase I analysis section 10.3.1. Bayesian credible intervals will be the 95% equal-tail intervals.

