##### Efficacy population

An evaluable patient for the study will be all patients randomised to Favipiravir or placebo (intention-to-treat).

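### The one Phase I population defined in this protocol requires a dose on favipiravir but only randomisation on SoC, which permits a one-sided exclusion if it is also used for the randomised secondary endpoints

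*Protocol*

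**What the plan says.** Protocol section 10.3.1 (Study population) gives a single definition of an evaluable Phase I patient: "all patients randomised to Favipiravir, who have had at least one dose or randomised to standard of care". It is not limited to particular endpoints.

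The phase it applies to is randomised 2:1 and controlled. Section 4.2.1 states: "Phase I will be open-label assessing escalating doses of IV Favipiravir compared with Standard of Care (SoC"). The synopsis (section 1.1) adds: "Each cohort includes 4 IV Favipiravir patients and 2 SoC". Section 3.1 lists as Phase I secondary endpoints the change in viral load up to Day 29, the WHO scale at Days 15 and 29, mortality at Days 15 and 29, and "Time from randomisation to death (up to day 29").

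For Phase II, section 10.3.2 (Efficacy population) uses the same opening phrase but a symmetric rule: "An evaluable patient for the study will be all patients randomised to Favipiravir or placebo (intention-to-treat").

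Two other statements in section 10.3.1 bear on the point. Under Decision Making: "Dose escalation will be based on review of safety data up to Day 8 on the safety population". That safety population is not defined in this protocol. Under Analyses: "Please refer to the AGILE master protocol phase I analysis section 10.3.1".

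**The concern.** A requirement to have received a dose is normal for a DLT or safety set, and the SoC arm has no dose to require. The difficulty comes when the same set is used to compare the arms on outcomes that run from randomisation.

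Take a patient who dies, deteriorates or withdraws after randomisation but before the first infusion. On SoC that patient stays in the analysis. On favipiravir the patient leaves it. A death in that interval counts in one arm and disappears from the other, although the endpoint's clock starts at randomisation in both. Because the phase is open label, a decision to withdraw or to withhold the first dose can also be taken with the allocation known.

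What is at stake is whether the reported Phase I between-arm summaries of viral load, WHO grade and mortality keep the protection of randomisation.

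**Working it through.** **1. Sample size in the plan.** Inputs: cohorts of 6, each with 4 favipiravir and 2 SoC; 5 cohorts planned and up to 2 more (sections 1.1 and 10.2).
- Planned: 5 × 6 = 30, which matches the plan; 5 × 4 = 20 favipiravir and 5 × 2 = 10 SoC.
- Maximum: 7 × 6 = 42, which matches the plan; 7 × 4 = 28 favipiravir and 7 × 2 = 14 SoC.

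**2. What the rule does to the denominators.** With u undosed favipiravir patients, the arms become (20 − u) against 10, or (28 − u) against 14. The SoC count never changes. One undosed patient removes 1/20 = 5.0% of the planned favipiravir arm, 1/28 = 3.6% of the largest one, and 1/4 = 25% of a cohort's favipiravir patients.

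**3. How often it could happen.** The protocol gives no non-dosing rate, so the rates r below are assumptions. Expected exclusions are n × r, and the chance of at least one is 1 − (1 − r)^n.

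| Assumed rate | Expected, n = 20 | At least one, n = 20 | Expected, n = 28 | At least one, n = 28 |
|---|---|---|---|---|
| 2% | 0.4 | 33% | 0.56 | 43% |
| 5% | 1.0 | 64% | 1.4 | 76% |
| 10% | 2.0 | 88% | 2.8 | 95% |

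**4. How far one exclusion could move a result.** Assume mortality of 10% among all randomised favipiravir patients; this figure is also not in the protocol. With u undosed patients whose mortality is d, the rate in the dosed patients is (n × 0.10 − u × d) / (n − u). For u = 1:
- n = 20, the undosed patient dies: (2 − 1)/19 = 5.3%, a shift of −4.7 points.
- n = 20, the undosed patient survives: 2/19 = 10.5%, a shift of +0.5 points.
- n = 28, the undosed patient dies: (2.8 − 1)/27 = 6.7%, a shift of −3.3 points.
- n = 28, the undosed patient survives: 2.8/27 = 10.4%, a shift of +0.4 points.
- Non-dosing unrelated to outcome (d = 0.10): (2 − 0.1)/19 = 10.0%, an expected shift of 0.

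Under an all-randomised rule the denominators stay at 20 and 10 (or 28 and 14), and the shift from exclusion is zero by construction.

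**The case against.** The strongest defence is that the rule serves Phase I's purpose. Both primary endpoints concern adverse events and DLTs, and section 9.1.1 defines a DLT by its relation to the study drug, so an undosed patient cannot contribute. This stands for those endpoints. It does not extend to endpoints counted from randomisation.

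A second defence is that assigning analysis sets to secondary endpoints can be left to the SAP or the Master Protocol. In part this stands: section 10.3.1 names a separate safety population and refers the Phase I analyses to a Master Protocol that is not at hand. A reader might infer that the dosed set is the only Phase I population there is. The documents support only that it is the only one defined in this protocol. Still, the text is a stated rule for the study and not a gap, and an SAP that followed it would inherit the asymmetry.

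Third, the window is short. Section 5.5 places randomisation after eligibility is confirmed, and section 8.2.1 has treatment start on the day of randomisation. This stands and keeps the likely number of undosed patients low. A reader might also infer from section 8.2.1 that the plan expects laboratory results to block dosing after randomisation. The wording, "results are required prior to dosing only if clinically indicated", relaxes a requirement. It leaves non-dosing possible but does not show that it is foreseen.

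Fourth, no between-arm test is stated for these endpoints, and with about 20 against 10 patients spread over several doses they can hardly be more than descriptive. This limits the harm without removing it, since a descriptive comparison of randomised arms is still read as one. For some patients the choice of set also makes no difference: one who withdraws before dosing may supply no later viral load under either rule.

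**Conclusion.** The point holds in a limited form, and its weight is minor. The Phase I definition is one-sided, it differs without explanation from the Phase II rule, and it does not fit secondary endpoints timed from randomisation if it is applied to them.

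Two stronger conclusions are tempting and not supported. One is that the Phase I comparisons are biased in favour of favipiravir. Bias needs at least one undosed favipiravir patient and a link between non-dosing and prognosis. The direction is plausible if sicker patients go undosed, but it is not established. The drop of 4.7 points is the extreme of a range that also runs to +0.5, and it requires one of the two assumed favipiravir deaths to fall between randomisation and first infusion. The other is that the Phase II decision is affected. The synopsis bases the Phase II dose on safety, tolerability and PK, section 10.3.2 refers to safety and tolerability, and escalation uses safety data to Day 8. No stated decision rule uses viral load, WHO grade or comparative mortality from Phase I.

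The harm is therefore confined to the reported Phase I between-arm summaries. Its size rests on the assumed non-dosing rates and the assumed 10% mortality.

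**What to change.** In section 10.3.1, define two sets:
- for viral load, WHO scale, mortality and time to death, all randomised Phase I patients analysed in the arm assigned, as section 10.3.2 does for Phase II;
- for DLT, safety and PK, keep the condition of at least one dose for favipiravir patients, and state whether this is the safety population named under Decision Making.

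Report the number of undosed patients by arm, with reasons, and check both definitions against the Master Protocol.

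The cost is a sentence or two here and the matching text in the SAP, with no new assessments. The visit schedule already counts Day 1 as the day of randomisation. Section 4.2.1.1, however, counts monitoring from the first dose, so the amendment should say that undosed patients continue on the schedule counted from randomisation.
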